#### Informed consent

The study will be discussed with the subject. The patient information sheet will be given to the patient at the screening visit, and the patient will be asked to contact us if he/she is willing to take part. A subject wishing to participate must give written informed consent prior to any study-related procedures or change in treatment. The participant must personally sign and date the latest approved version of the informed consent form before any study-specific procedures are performed. Written and verbal versions of the participant information and informed consent will be presented to the participants, detailing the exact nature of the study, the implications and constraints of the protocol, the known side effects, and any risks involved in taking part. It will be clearly stated that the participant is free to withdraw from the study at any time for any reason without prejudice to future care, and with no obligation to give the reason for withdrawal.

The participant will be allowed as much time as wished to consider the information, and the opportunity to question the investigator, their GP or other independent parties to decide whether they will participate in the study. Written informed consent will then be obtained by means of the participant’s dated signature and dated signature of the person who presented and obtained the informed consent. The person who obtained the consent must be suitably qualified and experienced and have been authorized to do so by the chief/principal investigator. A copy of the signed informed consent will be given to the participants. The original signed form will be retained at the study site, and an additional copy will remain in the patient notes.

#### Randomization

Subject numbers will be assigned sequentially as each subject enters the study.

The subjects will be assigned to a study treatment by a web-based random numbers generator using block randomization without minimization. This application will be specially designed for this study by the Department of Epidemiology, Biostatistics and Health Technology Assessment of the Radboud University Nijmegen Medical Center (Nijmegen, the Netherlands). Randomization will be performed at the same visit as the baseline visit. The randomization schedule is designed by a statistician, and the randomization codes are kept in the CRF and in the digital database of the Clinical Research Center Nijmegen (www.CRCN.nl).

#### Interventions

##### Half-dose PDT treatment

For this intervention, the patients need dilated pupils (dilation is achieved with 1.0 % tropicamide and 2.5 % phenylephrine). All patients will get an intravenous infusion of 3 mg/m^2^ verteporfin (Visudyne ™) (half-dose) over a period of 10 minutes. At exactly 15 minutes after the start of the infusion, an anesthetic eye drop is given (oxybuprocaine 0.4 % or equivalent), a contact lens (a Volk™ PDT lens) is positioned on the affected eye, and the aiming beam of the laser is focused on the treatment area. The magnification factor is taken into account in the settings of the PDT machine. The area of treatment is chosen, with the area of the aiming beam corresponding to the area of the subsequent laser spot area. The area that has to be treated is determined based on the hyperfluorescent area(s) on midphase (approximately 10 minutes) ICG angiography that correspond(s) to the SRF accumulation in the macula on the OCT scan and hyperfluorescent “hot spots” on the midphase (approximately 3 minutes) fluorescein angiogram. The spot size will be defined based on the diameter of the hyperfluorescent area on the ICG angiography plus 1 mm (Fig. 3). The edge of treatment spot has to be *at least 200 μm away from the optic disc rim*. The PDT treatment is performed with standard 50 J/cm^2^ fluency, a PDT laser wavelength of 689 nm, and a standard treatment duration of 83 seconds. Care must be taken to treat at *exactly* 15 minutes after the start of the infusion, to maximize the localization of the effect of treatment to the choroid and minimize possible damage to the adjacent retinal structures. The PDT treatment must take place at least 45 minutes after ICG angiography has been performed.

**Fig. 3 Fig3:**
[figure not shown]
Examples of areas treated in photodynamic therapy and micropulse laser treatment. Examples of imaging features on fluorescein angiography (FA) and indocyanine green angiography (ICG) angiography in chronic central serous chorioretinopathy (cCSC), and the corresponding treatment areas for photodynamic therapy (PDT) and high-density subthreshold micropulse laser treatment (HSML). **a-b** FA of the right eye of a patient showing hyperfluorescent “hot spots,” indicating leakage inferior of the fovea (**a**). On ICG angiography, an area of hyperfluorescence, which corresponds to the hyperfluorescent area on the FA, is seen (**b**). **c-f** An example of a PDT spot (white circle) overlapping the hyperfluorescent area on the ICG angiography plus 1 mm as described in the protocol (**c**). HSML treatment scheme that would apply to the same eye, in which only the central foveal area is excluded for treatment (white circle). The hyperfluorescent area on the ICGA is treated with numerous, nonoverlapping adjacent laser spots (white area) (**d**)

##### HSML treatment

For this intervention, the patients need dilated pupils (dilation achieved with 1.0 % tropicamide and 2.5 % phenylephrine). An anesthetic eye drop is given (oxybuprocaine 0.4 % or equivalent), and a contact glass (for instance a Volk™ area centralis lens) is positioned on the affected eye. HSML treatment with an 810 nm diode laser will be performed of the areas identified on midphase ICG angiography. Multiple confluent, adjacent (nonoverlapping) laser spots will be applied, covering the leakage area on midphase ICG angiography. The number of spots and number of zones treated depends on the extent of the leakage area(s) on midphase ICG. The area that has to be treated is determined based on those hyperfluorescent area(s) on midphase (approximately 10 minutes) ICG angiography that correspond(s) to SRF accumulation in the macula on the OCT scan and hyperfluorescent “hot spots” on the midphase (3 minutes) fluorescein angiogram (Fig. 3). The treatment will consist of small adjacent laser spots covering the designated area *keeping a distance of 500 μm from the foveal center (corresponding to a laser-free circular zone of 1000 μm diameter centered on the fovea)*.

The following *HSML treatment settings* will be used: a power of 1800 mW, a duty cycle of 5 %, frequency of 500 Hz, exposure time of 0.2 s per spot, a spot size of 125 μm, and a minimal distance of the spot from the fovea of 500 μm [48, 55]. 

Subthreshold treatment is desired, meaning that no visible reaction due to laser treatment has to be seen in the retina. In virtually all patients, a power of 1800 mW will not produce a visible discoloration of the retina after application of a laser spot with the aforementioned settings. If retinal discoloration is seen at a power of 1800 mW (corresponding to suprathreshold treatment), for instance in patients with darkly pigmented fundi, the power will be reduced with steps of 300 mW until there is no visible reaction. The first laser “test” spot will always be applied just outside the macular area.

#### Retreatment criteria and considerations

At evaluation visit 1, at 6 to 8 weeks after treatment, an OCT scan of the retina will be performed, among other imaging examinations. If there still is SRF present in the macular area, a second treatment will be performed according to the protocol within 3 weeks after evaluation visit 1.

This second treatment (either half-dose PDT or HSML treatment) will again be guided by the hyperfluorescent area(s) on the ICG angiography that correspond(s) to SRF accumulation in the macula on the OCT scan and the hyperfluorescent “hot spots” on the midphase (approximately 3 minutes) fluorescein angiogram.

In cases where there is no more SRF under the fovea but there is persistent fluid within the macular area encircled by the optic disc and temporal retinal vascular arcade, retreatment will be performed. The rationale behind this second treatment is that the persistent fluid may be interpreted as an incomplete treatment response because SRF accumulation indicates ongoing disease activity due to choroidal vascular hyperpermeability and fluid leakage through the RPE.

Note that if a patient did not require retreatment at evaluation visit 1 (=6-8 weeks after treatment visit 1) according to the protocol but returns with visual symptoms in the period between evaluation visit 1 and the follow-up visit at 7 to 8 months, a regular clinical examination should be performed that includes at least a measurement of visual acuity, ophthalmoscopy, and OCT scan to determine whether SRF has reoccurred. If there is evidence of recurrence of SRF on OCT (and therefore disease activity), these findings should be noted in the CRF. In these cases, additional evaluations compatible with evaluation visit 2 should be performed, and the patient should be planned for treatment visit 2 (max. 2 to 3 weeks after evaluation visit 2). Further evaluation will adhere to the retreatment criteria described above.

However, no treatment is allowed if the patient has already been treated twice (either with two half-dose PDT treatments or two HSML treatments) according to the trial protocol between evaluation visit 1/2 and follow-up visit (7 to 8 months after treatment visit 1). There are no data on the usefulness of more than two half-dose PDT treatments in the same patient with persistent cCSC. Some authors argue that more than two PDT treatments in the same eye may increase the risk of complications such as choroidal ischemia and the formation of choroidal neovascularization. In the case of HSML treatment, there also are no reports to suggest that more than two treatments may be useful. That is why a maximum amount of two of the same treatments is allowed within the trial period. After completion of the trial (at follow-up visit, 7 to 8 months after treatment visit 1), treatment may be considered and the treatment modality may be chosen at the discretion of the treating ophthalmologist.

#### Definition of end of trial

The end of trial is the date on which the last included participant has received the last follow-up visit (7 to 8 months after treatment 1).

#### Discontinuation and withdrawal of participants from study treatment

Each participant has the right to withdraw from the study at any time. In addition, the investigator may discontinue a participant from the study at any time if the investigator considers it necessary for any reason including the following:Ineligibility (either arising during the study or retrospective having been overlooked at screening).Significant protocol deviation.Significant non-compliance with study requirements.An AE that requires discontinuation of the study medication or results in inability to continue to comply with study procedures.Consent withdrawn.Lost to follow-up.Pregnancy before evaluation visit 1 or 2 (which is a relative contraindication for angiography). Pregnancy will not be routinely tested in female patients, but the possibility of pregnancy will be discussed during eligibility screening.

Patients suffering from a vision-threatening AE will also be withdrawn from the study. Withdrawal from the study will result in exclusion of the data from analysis from those participants, unless adherence to the protocol and follow-up examinations were sufficient to allow inclusion in the analysis. The reason for withdrawal will be recorded in the CRF.

If the participant is withdrawn due to an AE, the investigator will make arrangements for follow-up visits or telephone calls until the AE has resolved or stabilized.

Sample size calculations showed the need for 78 participants per treating arm to find significant values. In case of a withdrawal, a replacement subject will be included. This could cause a delay to the end of the trial but is not relevant for the outcomes. All subjects withdrawn from this study will return to normal consultation at their ophthalmologist of choice.

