## Methods/Design

### Summary of trial design

This study is a multicenter, prospective, randomized, controlled, open-label study that will compare the efficacy and safety of two treatments in patients with cCSC. The first group of patients will receive half-dose PDT treatment. The second group of patients will receive 810 nm HSML treatment. Each patient will receive at least one treatment but may be eligible to receive a second treatment during follow-up (Fig. 2), which will be the same type of treatment as the first treatment: either half-dose PDT treatment or HSML treatment.

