#### Procedures for recording adverse events/reactions

All AEs occurring during the study observed by the investigator or reported by the participant, whether or not attributed to study medication, will be recorded on the CRF. The following information will be recorded: description, date of onset and end date, severity, assessment of relatedness to study medication, other suspect drug or device and action taken. Follow-up information should be provided as necessary. AEs considered related to the study medication, as judged by a medically qualified investigator or the sponsor, will be followed until resolution or until the event is considered stable. AEs considered related to the study procedure, as judged by a qualified investigator or the sponsor, will be followed until resolution or until the event is considered stable. All related AEs that result in a participant’s withdrawal from the study or are present at the end of the study, should be followed up if the patient gives consent to do so, until a satisfactory resolution occurs.

It will be left to the investigator’s clinical judgment whether or not an AE is of sufficient severity to require the participant’s removal from the trial. A participant may also voluntarily withdraw from treatment due to what he or she perceives as an intolerable AE. If either of these occurs, the participant must undergo an end-of-study assessment and be given appropriate care under medical supervision until symptoms cease or the condition becomes stable.

The relationship of AEs to the study medication will be assessed by a medically qualified investigator, and if necessary, discussed with the chief investigator. Any pregnancy occurring during the clinical study and the outcome of the pregnancy fathered by trial participants, should be recorded and followed up for congenital abnormality or birth defect.

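### Withdrawn participants are left out of the analysis by default, under an undefined exception, and replaced, so the analysis set depends on events after randomisation and the comparison can be biased

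*Protocol article*

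**What the plan says.** The rule is in the protocol article, under Discontinuation and withdrawal of participants from study treatment. It has five parts:

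- **Investigator's discretion:** "the investigator may discontinue a participant from the study at any time if the investigator considers it necessary for any reason". The listed reasons include protocol deviation, non-compliance, adverse events and ineligibility discovered later.
- **Mandatory withdrawal:** "Patients suffering from a vision-threatening AE will also be withdrawn from the study".
- **Exclusion by default:** "Withdrawal from the study will result in exclusion of the data from analysis from those participants".
- **Exception:** the same sentence continues "unless adherence to the protocol and follow-up examinations were sufficient to allow inclusion in the analysis".
- **Replacement:** "In case of a withdrawal, a replacement subject will be included", followed by "This could cause a delay to the end of the trial but is not relevant for the outcomes".

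Three other sections bear on it. Summary of trial design describes a "multicenter, prospective, randomized, controlled, open-label study". Vision-threatening adverse events/reactions counts a loss of more than 30 letters within the 7 to 8 month follow-up as one criterion. Procedures for recording adverse events/reactions says that after removal or voluntary withdrawal for an adverse event "the participant must undergo an end-of-study assessment".

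The sections on statistical methods name no analysis set that would override the exclusion.

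**The concern.** Randomisation protects the comparison only if those analysed are those randomised, or if those missing are missing for reasons unrelated to arm and outcome. Here, inclusion depends on adherence, adverse events and follow-up after allocation.

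The link to outcome is most direct for visual acuity. A severe loss of letters triggers withdrawal, withdrawal triggers exclusion by default, and mean change in ETDRS visual acuity at 6 to 8 weeks and at 7 to 8 months is a secondary endpoint. If one treatment caused more such losses, its mean change could look better than it was.

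The primary endpoint is exposed to a lesser degree. Someone withdrawn before the first evaluation for an adverse event, deviation or non-compliance may be left out, and that may happen at different rates in the two arms.

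The exception does not settle this. No threshold for sufficient adherence or follow-up is given, and the judgement can be made with arm and result known. A replacement brings the arm back to 78, but the newcomer does not carry the outcome of the person who left. The statement that this is irrelevant to the outcomes is therefore wrong.

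**Working it through.** **Inputs from the article.** Two-sided α 0.05, 80% power, 78 per arm, 1:1 allocation, a 22-point planned difference, HSML success about 50%, one O'Brien-Fleming interim analysis.

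**Assumptions.** PDT success 72% (50% + 22 points; the article does not state the pair). An O'Brien-Fleming inflation of about 1.008. The withdrawal rates, and the share of failures among those withdrawn. The interim look is ignored in the rejection probabilities below.

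**1. The plan's own figure.** With mean rate 0.61:

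n = [1.96·√(2·0.61·0.39) + 0.8416·√(0.50·0.50 + 0.72·0.28)]² / 0.22² = 75.97, so 76 per arm.

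76 × 1.008 = 76.6, so 77, against the stated 78. Power at 78 per arm is 81.0%. The sample size reproduces and is not in dispute.

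**2. Type I error under selective exclusion.** Let p be the true success rate in both arms, w the fraction withdrawn from one arm, and f the share of those withdrawn who are failures. The arm is refilled to 78. Its expected rate is

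a = [p − w(1 − f)] / (1 − w).

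The rejection probability is that of the pooled two-proportion z-test comparing a with p. For p = 0.60, w = 0.10, f = 1: a = 0.60/0.90 = 0.667, the difference is 0.0667, the null and alternative standard errors are 0.0772 and 0.0770, and the rejection probability is 13.8%.

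| p | w (one arm) | f | Rate seen | Type I error |
|---|---|---|---|---|
| 0.60 | 5% | 100% | 63.2% | 6.9% |
| 0.60 | 5% | 80% | 62.1% | 5.8% |
| 0.60 | 10% | 100% | 66.7% | 13.8% |
| 0.60 | 10% | 80% | 64.4% | 8.8% |
| 0.60 | 10% | 60% | 62.2% | 5.9% |
| 0.60 | 10% | 40% | 60.0% | 5.0% |
| 0.60 | 15% | 100% | 70.6% | 28.3% |
| 0.65 | 10% | 100% | 72.2% | 16.2% |

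The row with f = 40% is withdrawal unrelated to outcome, because 40% of everyone fails when p = 0.60. If failures are excluded equally from both arms, type I error also stays at 5.0%.

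**3. Effect estimate at 72% versus 50%, f = 100%.** The true difference is 22.0 points and the true relative risk 1.44.

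- Exclusion from PDT only: 5% gives 0.72/0.95 − 0.50 = 25.8 points (relative risk 1.52); 10% gives 30.0 points (1.60).
- Exclusion from HSML only: 5% gives 0.72 − 0.50/0.95 = 19.4 points (1.37); 10% gives 16.4 points (1.30).
- Equal exclusion from both arms leaves the relative risk at 1.44.

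**4. Power if a missing OCT is counted as not resolved.** Both rates are multiplied by (1 − m), where m is the fraction missing per arm.

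- m = 0: 72% v 50%, power 81%.
- m = 5%: 68.4% v 47.5%, power 76%.
- m = 10%: 64.8% v 45.0%, power 70%.

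**5. Visual acuity.** No figure can be put on this endpoint. The article gives neither a standard deviation nor a rate of vision-threatening events.

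**The case against.** Several stronger readings are tempting, and the article does not support them.

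- **Everyone with a vision-threatening event is dropped.** Everyone with such an event is withdrawn, but the exception can keep their data. Someone whose event follows the 6 to 8 week OCT already has the primary outcome and can stay in that analysis. This stands.
- **The rule removes primary failures.** It does not do so directly. Under Retreatment criteria and considerations, persistent fluid at the first evaluation leads to a second treatment, not to withdrawal. Several grounds, such as pregnancy or withdrawn consent, are not defined by fluid status. Ineligibility overlooked at screening is a fact from before randomisation, although its discovery comes later. This limits the exposure of the primary endpoint but does not remove it.
- **The trial could not show harm.** Adverse events are still recorded on the case report form, a loss of more than 30 letters is a reportable serious adverse event, and the data monitoring committee reviews all of these. What can be biased is the comparison of mean visual acuity.
- **End-of-study data are thrown away.** The required assessment after an adverse-event withdrawal may itself make follow-up sufficient. The article does not say either way, and that is the weakness.
- **Type I error is 14% or more.** That needs withdrawal in one arm only and failure in all those withdrawn. Softer assumptions bring it close to 5%.

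After these concessions, the default exclusion, the undefined exception and the wrong statement about replacement all remain. None depends on an unseen analysis plan, because the article itself sets the rule.

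**Conclusion.** The concern holds in a limited form. The article makes inclusion in the analysis depend on events after randomisation, leaves the exception to undefined judgement in an open-label trial, and wrongly treats replacement as harmless. Visual acuity is the endpoint most at risk, because one of its worst values is itself a trigger for withdrawal. The primary OCT endpoint is exposed mainly through withdrawals before the first evaluation.

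The comparison can be biased; the article does not show that it will be. With 10% withdrawn from one arm and 60% true success in both, type I error runs from 5.0% to 13.8% according to how strongly withdrawal follows failure. At the assumed planning rates, one-arm exclusion of failures amounting to 5% to 10% of the arm moves the 22-point difference by about 3 to 8 points, in either direction. Size and direction depend on imbalance between arms and on the link to outcome, and the article gives no figure for either.

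**What to change.** Change the analysis rule only; the clinical rule on when a participant leaves treatment is not at issue.

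- Replace the exclusion sentence with: *All randomised participants are analysed in the arm to which they were randomised, and all data collected before and after withdrawal, including the end-of-study assessment, are used.*
- Delete the statement that replacement is irrelevant to the outcomes. State that any replacement is additional and that the withdrawn participant stays in the analysis set.
- Confine exclusion for poor adherence to a secondary per-protocol analysis.
- Prespecify the handling of a missing OCT at the first evaluation, with sensitivity analyses. Counting it as not resolved is one option; it can itself bias the comparison if missingness differs by arm.

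**Cost.** Wording and a little more analysis, with observed success rates that may look less favourable. If a missing OCT is counted as failure, the protocol should state the loss of power: from 81% to about 76% with 5% missing per arm, or 70% with 10%. If the trial instead recruits extra participants to offset missing outcomes, simple inflation gives 78/0.95 = 82.1, so 83 per arm, or 78/0.90 = 86.7, so 87 per arm.
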